### Outcome measurements

2.10

All outcomes, including the primary and secondary outcomes, will be evaluated before the intervention, at the end of the intervention, 8 weeks after the first intervention, and 4 weeks after completion of the intervention. We will exclude participants who completed less than 20 therapy sessions out of the 24 scheduled.

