### Study design

2.1

This study is a randomized controlled clinical trial with a prospective, outcome assessor-blinded, parallel-arm, 1:1:1 allocation ratio, single-center design. This study is a pilot study comparing the effect between “EA with computerized cognitive rehabilitation” and “tDCS with computerized cognitive rehabilitation” to investigate the effect and safety of combination therapy of EA or tDCS with computerized cognitive rehabilitation. Participants who meet the inclusion and exclusion criteria will be randomly allocated into a computerized cognitive rehabilitation treatment (CCRT) group (n = 15), combination therapy with EA and computerized cognitive rehabilitation treatment (CECCRT) group (n = 15), and combination therapy with tDCS and computerized cognitive rehabilitation treatment (CTCCRT) group (n = 15), for a total of 45 participants. The CCRT group will receive computerized cognitive rehabilitation therapy, the CECCRT group will receive combined EA and computerized cognitive rehabilitation therapy, and the CTCCRT group will receive combined tDCS and computerized cognitive rehabilitation therapy. All groups will receive therapy once a day for 3 days a week (excluding Saturdays and Sundays) for 8 weeks, giving a total of 24 therapies scheduled during the hospitalization period at Chonnam National University Hospital.

The outcomes will be measured before intervention, at the end of intervention, 8 weeks after the first intervention, and 4 weeks after completion of the intervention. The change in cognitive function as assessed using the Lowenstein occupational therapy cognitive assessment (LOTCA) scale will be measured as the primary outcome. The changes in the performance of every day movements will be measured using the Korean version of the modified Barthel index (K-MBI) and changes in health-related quality of life will be measured using the European Quality of Life Five Dimension Scale (EQ-5D-3L). The K-MBI and EQ-5D-3L will be secondary outcomes in this study.

This clinical trial was conducted by the Korea Health Industry Development Institute in 2018, a research project on the development of therapeutic techniques for the prevention of dementia and combination therapy with computerized cognitive rehabilitation (HI18C0546).

The design of this study is summarized in Figure 1. And time table of protocol is summarized in Table 1.

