### Study termination

2.13

Participants will be excluded from this study if adverse events (AEs) occur or the investigator believes that a procedure may cause AEs during the study.

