### Sample size estimation

2.15

Like the other pilot study, we calculated that 15 participants are required in each group, giving a total of 45 participants, in this clinical trial. A 25% of dropout rate was taken into consideration for a sample size of 12 per group.^[25]^ The CRC will manage the treatment schedule of subjects to minimize the dropout rate.

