### Statistical analysis

2.17

The statistical analysis will be conducted by a statistician who is not involved in this study and SPSS version 21 software (IBM Corp, Armonk, NY) will be used. We will analyze the general characteristics and outcome data at baseline, at the end of the intervention, and 4 weeks after intervention completion. Continuous variables will be presented as means and standard deviations or means and 95% confidence intervals. Independent *t*-test or Wilcoxon rank sum test will be used for continuous data and chi-squared test or Fisher exact test will be used for categorical data. The primary and secondary outcomes of the 3 groups will be measured using the changes in score at the end of the intervention and 4 weeks after the end of the intervention relative to the initially evaluated score. Each group will then be analyzed using a paired *t*-test or Wilcoxon signed rank test. A repeated measures analysis of variance, 2 sample *t*-test, Wilcoxon rank sum test can be used for the analysis of the degree of change at each outcome evaluation period. *P*-values <0.05 will be considered statistically significant.

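### Excluding randomised participants for fewer than 20 of 24 sessions (2.10) or for adverse events (2.13) limits the LOTCA comparison to adherent participants and can bias it

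*Protocol article*

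**What the plan says.** Two sections of the protocol article remove participants on events that can only occur after allocation.

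- **Outcome measurements (2.10)**, which covers the primary and secondary outcomes: "We will exclude participants who completed less than 20 therapy sessions out of the 24 scheduled".
- **Study termination (2.13)** adds a second rule: "Participants will be excluded from this study if adverse events (AEs) occur or the investigator believes that a procedure may cause AEs during the study". No severity grade or causal link is attached to this rule.

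The setting matters for who is likely to be removed:

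- Study design (2.1) describes a "parallel-arm, 1:1:1 allocation ratio, single-center design", with the schedule "giving a total of 24 therapies scheduled during the hospitalization period".
- Under Intervention (2.9), EA at eight sites or tDCS is added to CCRT in two arms; the third arm receives CCRT alone.
- Incidence of AEs (2.14) lists possible adverse events for EA and for tDCS, and none for CCRT alone.
- Under Blinding (2.8), participants know their treatment; only the outcome assessor is blinded.

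Statistical analysis (2.17) compares changes from baseline at the end of the intervention and 4 weeks later, and "values <0.05 will be considered statistically significant". It does not bring the excluded participants back. Sample size estimation (2.15) expects sizeable loss: "A 25% of dropout rate was taken into consideration for a sample size of 12 per group".

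**The concern.** Randomisation makes the three groups comparable at allocation. Removing people later, for reasons that may depend on the assigned arm and on how they are doing, can undo that. Someone who finds needling or stimulation hard to tolerate may miss sessions or report an adverse event; that route does not exist in the CCRT arm. If such people would also have shown a different change in LOTCA, the retained groups differ even when the add-on treatment does nothing.

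The contrast of each combination arm with CCRT alone is at stake, as is the contrast between the two combination arms, since their procedures and listed adverse events also differ. Excluded participants have no stated role in the analysis, so the plan as written offers no comparison that would reveal the bias.

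**Working it through.** **1. The plan's own loss figure.** 12 per group with a 25% allowance: 12 × 1.25 = 15 per group, 3 × 15 = 45 in total. This reproduces the stated size. Dividing by the retained fraction instead gives 12 / 0.75 = 16, and 15 × 0.75 = 11.25. That difference is a separate, minor point and nothing below depends on it. The relevant fact is that the plan itself foresees losing a material fraction of each arm.

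**2. The threshold.** 20 / 24 = 83.3%. A participant may miss four sessions and stay; missing five removes them.

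**3. Size of a possible bias.** The document gives no exclusion rate by arm, no link between adherence and LOTCA change, and no SD for LOTCA change. The inputs here are therefore assumptions:

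- no true treatment effect;
- LOTCA change in SD units, with correlation r with a normally distributed adherence tendency, the same in each arm;
- the lowest fraction a of an add-on arm and the lowest fraction b of the CCRT arm are excluded.

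The mean change among those kept, when a fraction e is excluded, is r × φ(z_e) / (1 − e), where z_e is the e-quantile and φ the density of the standard normal. The bias is

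r × [φ(z_a)/(1 − a) − φ(z_b)/(1 − b)].

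With a = 0.25 and b = 0.10, the two terms are 0.424 and 0.195, a difference of 0.229.

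| r | Bias (SD of LOTCA change) |
|---|---|
| 0 | 0 |
| 0.3 | 0.3 × 0.229 = 0.07 |
| 0.7 | 0.7 × 0.229 = 0.16 |

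With a = b the bracket is zero, so the bias is zero for any r. With r negative, where those removed would have done better, the same figures apply with the opposite sign.

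**4. Check by simulation.** 20,000 trials per setting, 15 per arm, no true effect, two-sided pooled t-test at 5%:

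| Excluded, CCRT vs add-on | r | Bias (SD) | Type I error |
|---|---|---|---|
| 20% vs 20% | 0.3 or 0.5 | about 0 | about 5% |
| 6.7% vs 20% (1 vs 3 of 15) | 0.3 | 0.06 | 5.1% |
| 6.7% vs 20% | 0.5 | 0.11 | 5.6% |
| 6.7% vs 33.3% (1 vs 5 of 15) | 0.3 | 0.12 | 5.9% |
| 6.7% vs 33.3% | 0.5 | 0.20 | 7.2% |

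Simulated and analytic biases agree to within 0.003 SD in the unequal settings shown.

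**5. Scale.** With 12 per arm the standard error of a two-arm difference is √(2/12) = 0.41 SD. A bias of 0.07 to 0.16 SD is 0.17 to 0.39 of one standard error (0.07/0.41 and 0.16/0.41).

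**The case against.** The strongest reply is that the sentence in 2.10 does not say what people are excluded from. It stands among the outcome measures, is not repeated in 2.17, and could be a per-protocol definition. This is also a condensed article, and a fuller document may define other analysis sets. The ambiguity is real, and the lack of an all-randomised analysis in an article is not in itself a fault. But the exclusion is stated, it applies to all outcomes, and the text shown gives no other set. A later document that analysed everyone would have to contradict it as written.

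A second reply is that this is a pilot, that loss is already budgeted, and that the illustrated bias is well under half a standard error. Those facts are correct and they temper the size. They do not remove the problem: significance testing is planned, and a larger randomised number does not correct selective loss.

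A reader might infer more than the documents support:

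- *That only full completers are analysed.* The cut-off is 83% of sessions.
- *That the session rule is the sole route of removal.* Section 2.13 is a second one, and an amendment to 2.10 alone would conflict with it.
- *That the bias must favour EA or tDCS.* That needs those removed to be poorer responders, which is assumed.
- *That early discharge drives the loss.* Sessions are scheduled during hospitalisation, but discharge is nowhere given as a reason for missed sessions. It could reflect good recovery and reverse the sign, and nothing suggests it would differ by arm.
- *That the bias is larger.* Excluding 40% versus 5% gives 0.16 to 0.37 SD by the same formula, but nothing in the document points to so extreme a split.

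**Conclusion.** The concern holds. Sections 2.10 and 2.13 both remove randomised participants on post-randomisation events. The document gives good reason to think removal may differ by arm: the added procedures, their listed adverse events, and participants' knowledge of their treatment. Followed as written, the plan compares adherent participants, and the LOTCA contrast can be biased.

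The size and sign cannot be determined from the document. Under the assumptions of no true effect, 25% versus 10% excluded, and a correlation of 0.3 to 0.7, the bias is about 0.07 to 0.16 SD. It is zero if exclusion is unrelated to outcome or acts equally in all arms. The conclusion rests on the rules as worded, not on these figures.

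**What to change.** Replace the exclusion sentence in 2.10 with:

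*All randomised participants are assessed at the end of intervention and 4 weeks later and are analysed in the arm assigned, whatever the number of sessions completed. An analysis limited to participants with at least 20 sessions is a sensitivity analysis only.*

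Reconcile 2.13 with this, so that leaving treatment after an adverse event does not mean leaving outcome assessment or the analysis. This concerns assessment and analysis only; when treatment should stop is a clinical matter on which no change is proposed here.

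The target analysis number becomes the 15 per group randomised (45 in total), not the 12 per group (36) allowed for. No significance level or recruitment figure changes. The costs are protocol wording, outcome visits for participants who stop or miss sessions, and some dilution of the estimated effect by non-adherence. Participants who decline those visits will still have missing outcomes.

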### Secondary outcomes

2.12

In this protocol, changes in K-MBI and EQ-5D-3L will be used as secondary outcomes. K-MBI is a modified assessment tool to evaluate the performance in activities of daily living in a Korean population that uses 10 items. The K-MBI items include personal hygiene, bathing, eating, toilet use, ability to climb stairs, ability to dress, bowel/bladder function, walking function, ability to get into and out of a chair/bed, and mobility. The score ranges from 0 to 100 and a higher score reflects better performance.^[22]^

EQ-5D-3L is a self-completed instrument for the assessment of health-related quality of life. Using the EQ-5D-3L, we can measure participants’ health-related quality of life and wellbeing using 5 dimensions: mobility, self-care, usual activities, pain, and anxiety/depression. Each dimension has 3 possible response options corresponding to no problems, some problems, or severe problems. Participants rate their overall health state on a 0 to 100 hash-marked, Vertical Visual Analogue Scale, with a higher score representing a better health state.^[23]^

### Study termination

2.13

Participants will be excluded from this study if adverse events (AEs) occur or the investigator believes that a procedure may cause AEs during the study.

### Incidence of AEs

2.14

During the study, all unexpected and unintended signs, symptoms, or diseases refer to AEs. During this period, all AEs reported by participants or the investigator will be recorded in detail, such as when the AEs occur, duration of symptoms, degree of severity (mild, moderate, or severe),^[24]^ any measures related to the AEs, time of AEs disappearance, and any potentially causal relationship between the treatment and AEs. All AEs will be reported to the principal investigator and Institutional Review Board and will be documented.

The possible AEs of EA include nausea, vomiting, skin irritation, bleeding, local hematoma, pallor, sweating or dizziness, fainting, headache, and infection, and AEs of tDCS may be pallor, pain, anxiety, sweating or dizziness, fainting, headache, and itching.

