**Discussion::**

This study aims to examine the effect and safety of combination therapy with EA or tDCS and CCRT in patients with VCI. This study can be useful in developing new treatment technologies using collaborative research with combined traditional Korean and conventional medicines.

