## Discussion

3

This protocol is designed to explore the synergistic effect of combined EA and CCRT therapy in the treatment and prevention of cognitive impairment caused by cerebrovascular disorders. In this protocol, we follow the Recommendations for Interventional Trials (SPIRIT) and Consolidated Standards of Reporting Trials (CONSORT) 2010 guidelines.^[26]^ For the evaluation of each therapy, the outcome measurements include the LOTCA, K-MBI, and EQ-5D-3L. The LOTCA is one of the most commonly used qualitative tools in the evaluation of cognitive function in cerebrovascular disease. Therefore, we will use changes in the LOTCA scale as the primary outcome, with changes in the K-MBI and EQ-5D-3L scores as secondary outcomes. Through this clinical trial, we expect to find that EA or tDCS with CCRT is safe and effective for patients with VCI.

This protocol has some limitations. First, we cannot perform a double blinded study because the practitioners know which procedure is applied to which participant. Second, we cannot use a multi-center pilot study and large sample size design due to the limited research funds. Third, we cannot apply another procedure other than EA and tDCS due to the small sample size and lack of adequate preliminary studies.

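### The adverse-event definition in 2.14 requires an event to be unexpected, which contradicts the list of foreseen EA and tDCS reactions that the same section calls AEs

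*Protocol article*

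**What the plan says.** Section 2.14 (Incidence of AEs) contains the article's only definition of an adverse event: "all unexpected and unintended signs, symptoms, or diseases refer to AEs". It then sets the recording rule, "all AEs reported by participants or the investigator will be recorded in detail", and among the details to be recorded is "any potentially causal relationship between the treatment and AEs". The reporting rule is "All AEs will be reported to the principal investigator and Institutional Review Board and will be documented".

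The second paragraph of 2.14 names reactions that are anticipated. For EA: "The possible AEs of EA include nausea, vomiting, skin irritation, bleeding, local hematoma, pallor, sweating or dizziness, fainting, headache, and infection". For tDCS: "AEs of tDCS may be pallor, pain, anxiety, sweating or dizziness, fainting, headache, and itching". No list is given for computerized cognitive rehabilitation (CCRT) alone.

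Safety is an aim of the trial. The Discussion part of the abstract says "This study aims to examine the effect and safety of combination therapy with EA or tDCS and CCRT in patients with VCI", and section 2.1 states the same purpose. Section 3 adds "we expect to find that EA or tDCS with CCRT is safe and effective". Section 2.13 (Study termination) uses the term AE as a trigger for excluding participants from the study.

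**The concern.** The definition joins two conditions, unexpected and unintended, so on its wording an event must meet both. Whether an event was foreseen is normally a separate attribute of an AE, used for reporting purposes, and does not decide whether the event counts. Here it sits inside the definition, directly above a list of reactions that the protocol foresees and still calls AEs.

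The ambiguity is not neutral between arms. A headache during CCRT alone is on no list, so it is plainly unexpected and meets the definition. The same headache under EA or tDCS is on the list, so a literal reader could leave it out. The people making that judgement would know the arm, and the protocol already states that it expects the combinations to be safe. Any loss of events would therefore tend to favour the anticipated conclusion on a stated aim.

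**Working it through.** There is no figure in the plan to reproduce: the article gives no AE rate, observed or assumed. The check is a comparison of texts.

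**1. Count the foreseen reactions in 2.14**, taking sweating or dizziness as one entry.

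| Listed for | Entries | Count |
|---|---|---|
| EA only | nausea, vomiting, skin irritation, bleeding, local hematoma, infection | 6 |
| tDCS only | pain, anxiety, itching | 3 |
| Both EA and tDCS | pallor, sweating or dizziness, fainting, headache | 4 |
| CCRT alone | none listed | 0 |

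EA: 6 + 4 = 10. tDCS: 3 + 4 = 7. Distinct entries: 6 + 3 + 4 = 13.

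**2. Apply the definition to the list.** Each of the 13 is foreseen by being listed, so each fails the unexpected condition for the treatment under which it is listed. The list calls all of them AEs. The two paragraphs give opposite answers for every listed reaction.

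**3. Ask whether the other sentences resolve it.** The recording and reporting rules apply to all AEs. They use the defined term, so they reach only as far as the definition does. The causality field is completed once an event has been classed as an AE. These sentences show intent, but they do not widen the definition.

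**4. Ask who would apply it.** Under 2.6 the envelopes are opened in front of the participant and the clinical research coordinator. Under 2.8 only the outcome assessor is blinded. Under 2.16 the coordinator records the data. Classification is therefore made with the allocation known.

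**5. Ask whether a size can be given.** If the true per-arm rate of a listed reaction is p and a fraction s of such events is left out in a combination arm, the recorded rate there is p × (1 − s). The article gives neither p nor s, and s may be 0. As an assumed illustration only, take p = 20% in each arm of 15, that is 3 events:

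- s = 0: 3/15 recorded, exact 95% interval 4.3% to 48.1%
- s = 1/3: 2/15 recorded
- s = 2/3: 1/15 recorded
- s = 1: 0/15 recorded, exact 95% interval 0 to 1 − 0.025^(1/15) = 21.8%

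The outcome runs from no effect to complete loss, depending on a fraction that nothing in the article fixes. This shows the direction and the limits; it is not an estimate.

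**The case against.** The strongest reply is that 2.14 answers the point itself. It expressly calls the listed reactions AEs, and a specific classification is at least as likely to govern as a loosely worded general sentence. The definition does not contain the word *only*, and no sentence leaves a listed reaction unrecorded. Severity, duration, measures taken and causal relationship are all to be recorded, which points towards capture. Section 2.13 also speaks of a procedure that the investigator believes may cause AEs, so the protocol uses the term for foreseeable events elsewhere. On this view the definition simply means effects that the treatment did not set out to produce.

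Much of this stands. A reader might infer that the plan removes expected reactions in the EA and tDCS arms and so understates harm there. The article does not support that: it has one definition and one recording procedure for all arms, and it names the listed reactions as AEs. A contrast such as 0/15 against 3/15 needs both an assumed event rate and complete suppression, neither of which the article states.

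What does not stand is the conclusion that nothing needs correcting. If the authors meant to capture these reactions, as the list suggests, then the definition does not say what they meant, and the definition is the text that staff would look up.

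**Conclusion.** The definition in 2.14 is wrong as written, measured against the list in the same section. This is an internal contradiction, and it is not a matter that an article would ordinarily leave to a fuller document.

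The consequence is a conditional risk. Foreseeable reactions could go unrecorded if staff who know the allocation apply the first sentence literally. In that case any under-count would tend to fall in the two combination arms, because only EA and tDCS have listed reactions. That is not an established bias, and its size cannot be derived. The conclusion rests on reading the two adjectives as joint conditions, which is their plain sense, and on the four reactions common to both lists being able to occur under CCRT alone as well.

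The point still deserves action, because safety is a stated aim and because section 2.13 makes exclusion depend on the same term. While the term is unclear, that rule cannot be applied consistently.

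**What to change.** In 2.14, define an AE as any unfavourable or unintended sign, symptom or disease during the study, whether or not it is expected or related to treatment. State that it is recorded identically in all three arms. Keep the list of anticipated reactions as information, and add expectedness to the AE form as a separate attribute beside the causal relationship already recorded.

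Reconcile section 2.13 with the corrected definition, so that both sections use the term in the same sense. The content of the clinical rule in 2.13 is for the investigators to settle.

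The cost is one sentence in 2.14, one added field on the AE form and a consistency check of 2.13. No extra visits or participants are needed. The downside is that recorded AE rates in the combination arms may look somewhat less favourable.
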